### **3.3.5 Sample size**

This study is designed to detect a doubling (100%) of the proportion of adolescent visits that had BP screening done (conservatively calculated in STATA version 16 as an increase from 17% to 34%) between the intervention and control groups. It is based on the assumption of a 2-sided test with 80% power at a 5% significant level, cluster sizes of 20 adolescents and an intra-cluster correlation coefficient (ICC) of 0.05. Accordingly, two groups of ten (10) health facilities will be needed at the minimum. As this sample size estimation does not account for any potential loss to follow-up, we will recruit additional two facilities per arm (24 in total). Thus, a total of about 96 health workers (4 per facility) and about 480 adolescents living with HIV (20 per facility) will be enrolled in this study.

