### **3.3.6 Randomization**

**a. Sequence generation:** The unit of randomization will be the health facility. Randomization will be performed by a statistician independent of the study team, using computer-generated random permuted blocks and will be stratified by type of health facility (regional, district/ municipal, Polyclinic, Health Centre). Twelve facilities will be in the intervention arm and the rest in the control arm. The study statistician will provide each facility with a computer-generated list of random numbers to select a sample of 20 adolescent clients to participate in the baseline and end-line survey.

**b. Allocation concealment**: Each facility will eventually become aware of its allocation, but allocation will be concealed until the baseline assessment is completed. Adolescents will not be allocated to alternative interventions within a facility, so allocation concealment will not be an issue.

**c. Implementation of clusters:** The PI will provide the list of prospective facilities by type to the study statistician, anonymized by an ID**.** The study statistician will generate the random sequence and allocate practices to two separate dummy-coded groups without knowing which group will receive the intervention; the study statistician will remain blind to allocation until the collected follow-up data. Random allocation of clusters to intervention or control will occur consecutively as practices are recruited until the target sample size (24) is reached.

**d. Blinding:** Given the nature of the intervention, healthcare workers will inevitably be aware of their allocation and thus, blinding participants will not be possible. Each facility will also become aware of allocation. However, facilities will not be informed of allocation until after both facilities and individual health workers are identified and recruited (i.e., not until after baseline assessment). Adolescents within each facility will remain blind to allocation. The outcome assessors will be kept blind to the allocation. The facility contact that will use the random sequence of numbers to identify the sample of 20 patients within each facility will possibly not be blind to allocation. Blinding the entire research team is also impossible as intervention facilities will be contacted to arrange the sessions. However, the study statistician conducting the outcome analysis will remain blinded to allocation until after the outcome data have been collected at follow-up.

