### **3.4.2 Data Analysis**

Data will be analyzed using STATA 16. Summaries of variables will be obtained using frequencies, means and standard deviations. Histograms, bar graphs and box and whisker plots will be used to check for skewness and identify outliers. Proportions and frequencies will be used to summarise all binary or categorical variables. Means and standard deviations will be used to summarise continuous variables and proportions and frequencies for categorical variables. Chi-square tests will be used to determine associations between categorical variables. Independent sample t-tests or one-way ANOVA will be used to test for differences in means, and a z-test used to assess the difference in proportions. Simple and multiple logistic regression analysis will be carried out between outcome variables (binary) and other variables identified as potential confounders to test for the magnitude and strengths of associations. All tests will be two-tailed and statistical significance set at 0.05.

[figure not shown]

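### The analysing statistician's blind is guaranteed only until follow-up data are collected, so the protocol permits unblinding before the analysis

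*Protocol*

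**What the plan says.** Protocol section 3.3.6 describes the statistician's blind in two places.

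- Under c (implementation of clusters), the statistician is to "allocate practices to two separate dummy-coded groups without knowing which group will receive the intervention". The sentence continues: "the study statistician will remain blind to allocation until the collected follow-up data". A verb is missing, but the apparent meaning is that the blind lasts until the follow-up data have been collected.
- Under d (blinding), the protocol accepts that health workers and facilities will know their allocation, that the whole research team cannot be blinded, and that the facility contact who draws the patient sample may not be blind. As a counterweight it offers that "the study statistician conducting the outcome analysis will remain blinded to allocation until after the outcome data have been collected at follow-up".

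Outcome assessors have their own, separate blind.

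Section 3.4.2 lists the analyses: chi-square tests, t-tests or ANOVA, a z-test for a difference in proportions, and simple and multiple logistic regression between binary outcomes and "other variables identified as potential confounders to test for the magnitude and strengths of associations". It names no confounder and gives no rule or time point for identifying them.

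**The concern.** A statistician's blind is meant to stop knowledge of the arms from influencing how the data are analysed: which model is reported, which covariates go in, how awkward records are handled. A guarantee that lapses when data collection ends covers the period before any of those choices is made and leaves the choices themselves uncovered.

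This matters more here than in a trial with blinded participants, because the protocol concedes that most other blinds are impossible and presents this one as the remaining protection. At stake is the credibility of the arm comparison. If the codes were broken first, a reader could not tell whether an adjusted result was chosen before or after its direction was known.

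**Working it through.** The point is about wording and carries no figure of its own, so the check is mainly a comparison of passages.

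**Step 1: when does the guarantee end?** In 3.3.6 d it ends after the outcome data are collected at follow-up. In 3.3.6 c it ends at the same point, as far as the broken sentence can be read. Neither mentions database lock, fixing of the model or completion of the analysis, and no other section extends the blind.

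**Step 2: what does the statistician do before and after that point?** Before it, 3.3.6 a and c have the study statistician generating the sequence and supplying each facility with random numbers for sampling adolescents. After it, the task that 3.3.6 d names is the outcome analysis. The guaranteed blind therefore covers the first set of tasks and not the second.

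**Step 3: are analytic choices open on the text shown?** Section 3.4.2 lists several tests and a logistic model whose covariates are described only as "other variables identified as potential confounders". On this document alone, the covariates could be settled before or after the codes are broken.

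**Step 4: what would dummy codes protect, and what not?** Write the arm effect in a regression as b with standard error s, so that t = b/s. Swapping the two arm labels changes b to −b and leaves s unchanged, so |t| and the two-sided p-value stay the same for every covariate set. Section 3.4.2 specifies two-sided testing: "All tests will be two-tailed and statistical significance set at 0.05". It follows that:

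- coding the arms prevents choices guided by which arm is favoured;
- coding does not prevent a search for the smallest two-sided p-value, because someone holding only the codes can run the same search;
- that search is prevented only by fixing the model before outcomes are seen by coded arm.

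Both safeguards are needed, and the order matters: model first, then coded analysis, then unblinding.

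**Step 5: does this touch the sample size?** Section 3.3.5 assumes 17% against 34%, a "2-sided test with 80% power at a 5% significant level", 20 adolescents per facility and an ICC of 0.05. The design effect is 1 + (20 − 1) × 0.05 = 1.95. With unpooled variance, n per arm = (1.960 + 0.842)² × (0.17 × 0.83 + 0.34 × 0.66) / 0.17² = 99.3. Then 99.3 × 1.95 / 20 = 9.68, which rounds up to the stated 10 facilities per arm. With pooled variance, 103 × 1.95 / 20 = 10.04, and power at 10 per arm is 0.802. The plan's figure reproduces, and nothing in it depends on when the blind ends.

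**The case against.** The strongest reply is that the wording in 3.3.6 d sets a lower bound. It does not say that the codes are broken before the analysis, before lock or before the model is fixed, and the trial may well keep them longer. That stands. A reader might infer that the analysis will be done unblinded, and the document does not support that. It supports only that unblinding at that point is permitted.

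A reader might also infer that the confounders will be picked after unblinding. Section 3.4.2 gives no timing. A covariate list is commonly left to a statistical analysis plan, which may exist and is not shown. The missing list is therefore not the point here. Section 3.4.2 also names a z-test for proportions, which has no covariates and would fit the first hypothesis in section 1.10, so it is not established that the main arm comparison depends on covariate choice at all.

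Finally, a reader might attach an inflated false-positive rate. In null simulations with 24 facilities and 3 or 5 assumed covariates, choosing the smallest two-sided p-value over covariate sets gave 8.2% to 14.7% instead of about 5%. The rates were identical with the arm labels swapped, as Step 4 predicts. They measure unrestricted model choice, not the end of the blind. The covariates and the facility-level regression in those simulations are also not in the protocol, so no such figure belongs to this point.

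The other safeguards in 3.3.6 deserve credit: coded groups, blinded assessors and allocation withheld until after baseline. None of them covers the analysis stage. A statistical analysis plan that fixed the covariates would reduce the consequence but would not correct the end point that the protocol itself states.

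**Conclusion.** The point holds in a limited form. The protocol states an end point for the analysing statistician's blind, and that end point falls before the work the blind should protect. Unblinding before the analysis is permitted, not planned, and nothing in the protocol rules out choices made with the arms known. No numerical size can be given, because the document fixes neither the candidate covariates nor the timing.

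The conclusion assumes that no other document extends the blind. If a statistical analysis plan keeps the codes until the primary analysis is run, only the protocol's wording needs to be brought into line. This is a free improvement; the sample size and the design are unaffected.

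**What to change.** Replace the two statements in 3.3.6 c and d with one consistent rule, for instance:

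> The adjustment set and the primary model are fixed in writing before the study statistician sees any outcome by coded arm. The statistician analyses the primary and secondary outcomes on the dummy-coded groups. The codes are broken only after the database is locked and the primary analysis has been run and dated.

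This also repairs the incomplete sentence in 3.3.6 c. The cost is a few lines of text. The dummy codes already exist, and the key can stay with a member of the research team who must know the allocation anyway to arrange the intervention sessions. For the blind to hold in practice, the process measures in Table 1 that exist only for intervention facilities should be kept out of the statistician's file until the codes are broken.

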### **3.3.7 Intervention**

The 12 intervention facilities will receive a multi-component intervention package based on the theory of planned behaviour as captured in ***table 3.1***. They will be oriented on the risk of hypertension among adolescents living with HIV, be provided monthly feedback on their performance for the initial three months and receive the support of an opinion leader in their facility. They will also be provided with clinical decision support and sphygmomanometers with paediatric cuffs. The Fidelity of intervention delivery will be assessed using the process measures captured in ***table 3.1*** across the TPB domains.

### **3.3.8 Comparator**

All 24 facilities will be given an orientation on the guidelines for screening and managing hypertension among children and adolescents. This will be done by trained facilitators using PowerPoint presentations, group discussions and case scenarios.

**Table 1** **Application of Theory of Planned behavior to intervention design and measurement**

| **TPB Constructs** | **Intervention package** | **Process Measures** |
| --- | --- | --- |
| Attitude | 1. Orientation on hypertension risk among adolescents living with HIV | Pre and post-test scores |
| Subjective norms | 1. Audit and feedback 2. Opinion leaders 3. Patient education 4. Reminders(posters) | 1. The proportion of planned feedback sessions undertaken 2. The proportion of planned engagement sessions with opinion leaders held 3. The proportion of planned patient education sessions held 4. The proportion of expected posters pasted |
| Perceived behavioral control | 1. Provision of a paediatric sphygmomanometer 2. Orientation on BP measurement technique 3. Provision of clinical decision support | 1. The proportion of intervention facilities with paediatric sphygmomanometer 2. a.Proportion of target staff oriented on BP measurement technique   b. change in accuracy of BP measurements post-orientation   1. The proportion of intervention facilities with clinical decision support pack |

### **3.3.9 Outcomes**

#### **a. Primary outcomes**

The primary outcome will be the effect of the intervention on healthcare workers’ adherence to the guideline. It will assess adherence to recommendations on the

1. frequency of screening
2. Detection of elevated or high BP,
3. Investigation of high BP and
4. Management of elevated or high BP.

These will be assessed using a data extraction tool based on the HIV client care booklet. The tool will extract the data from the client care records of adolescents who received care within the period of interest. At baseline, it will assess the records of 20 randomly selected adolescents who received care at the facility six months prior to the assessment and extract the data from their most recent visit. At follow up, data will be extracted from the most recent visit of 20 randomly selected adolescents who received care at the facility after the intervention commenced.

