## **1.10 Study hypothesis**

The hypotheses that will be tested in the study are as follows:

1. There is no difference in the proportion of adolescent ART visits that had BPs checked between facilities exposed to the intervention and unexposed facilities.
2. There is no change in arterial stiffness parameters of hypertensive adolescents living with HIV after six months of exposure to the TPB- based intervention.

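### Four adherence domains are listed as primary without a composite, order or denominator, but only BP checking at a visit is hypothesised and powered

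*Protocol*

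**What the plan says.** Protocol 3.3.9a, under a heading in the plural, states: "The primary outcome will be the effect of the intervention on healthcare workers’ adherence to the guideline". Four domains follow:

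- "frequency of screening"
- "Detection of elevated or high BP"
- investigation, limited to high BP
- "Management of elevated or high BP"

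No score combines them, none is ranked first, and none has a stated denominator. All four are to be extracted from the client care record of one visit, the most recent, for 20 randomly selected adolescents per facility. On the data extraction form, systolic and diastolic BP are each either a value or marked as not recorded.

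The other sections are narrower. The only adherence hypothesis in 1.10 reads: "There is no difference in the proportion of adolescent ART visits that had BPs checked between facilities exposed to the intervention and unexposed facilities". The second hypothesis there concerns arterial stiffness. Section 3.3.5 says the study is "designed to detect a doubling (100%) of the proportion of adolescent visits that had BP screening done", from 17% to 34%. Section 3.4.2 adds one general rule: "All tests will be two-tailed and statistical significance set at 0.05".

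**The concern.** Sections 1.10 and 3.3.5 describe a trial with one primary endpoint, whether BP was checked. Section 3.3.9a describes four, three of which have neither a hypothesis nor a power calculation. As written, the document does not settle whether an effect on management without an effect on screening would make the trial positive, or the reverse.

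The last three domains raise a second difficulty. In a care record, detection, investigation and management of raised BP can be seen only where someone measured the BP, wrote it down, and it was raised. The intervention (feedback, opinion leaders, paediatric cuffs, decision support) is meant to increase measurement. If these domains are analysed among records with a raised BP, membership of the denominator is decided after randomisation by something the intervention changes. The intervention arm would then include adolescents who would have gone unmeasured under control, and the two groups need not be alike. The groups would also be very small.

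**Working it through.** **Inputs.** From 3.3.5: 17% vs 34%, two-sided 5%, 80% power, 20 adolescents per facility, ICC 0.05, 10 facilities per arm needed and 12 recruited. From 3.4.2: 0.05 for all tests. Taken as assumptions from the literature review, not as design values: hypertension in 10.5% of adolescents living with HIV in one study (2.5.4); in the pooled African data (2.4.1), BP at or above the 95th percentile in 5.5% and between the 90th and 95th in 12.7%.

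**1. Which endpoint the sample size belongs to.**
- Two proportions, pooled variance, 17% vs 34%: 103 per arm before clustering.
- Design effect: 1 + (20 − 1) × 0.05 = 1.95.
- 103 × 1.95 = 201 per arm; 201 / 20 = 10.04 facilities, against 10 stated. Power with 10 facilities per arm is 80.2%.

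The stated figure reproduces, for BP checking alone.

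**2. Error rate if the four domains were tested separately at 0.05.**
- Independent tests: 1 − 0.95⁴ = 0.185.
- Upper bound under any dependence, each test having true size 0.05: 4 × 0.05 = 0.20.
- Positive correlation usually lowers it, and very sparse data can. With 4 vs 9 records in each of the last three domains, true rates of 20% to 50%, independence and no clustering, the family-wise rate is about 14–17% with a z-test and 6–8% with Fisher's exact test.

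**3. Cost of keeping four co-equal primaries.** At a Bonferroni level of 0.05 / 4 = 0.0125, BP checking alone needs 146 × 1.95 = 285 per arm; 285 / 20 = 14.2, so 15 facilities per arm. At that level power is 61.8% with 10 facilities per arm and 71.7% with 12.

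**4. Expected records with a raised BP at follow-up.** Each arm has 12 × 20 = 240 adolescents. Records with any BP: 240 × 0.17 = 40.8 (control) and 240 × 0.34 = 81.6 (intervention). Multiplying by prevalence:

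| BP category (assumed prevalence) | Control | Intervention |
| --- | --- | --- |
| High, 5.5% | 2.2 | 4.5 |
| High, 10.5% | 4.3 | 8.6 |
| Elevated or high, 5.5% + 12.7% = 18.2% | 7.4 | 14.9 |
| Elevated or high, 30% (arbitrary upper value) | 12.2 | 24.5 |

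The first two rows apply to investigation, which is limited to high BP. The last two apply to detection and management.

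**5. What such numbers can show.** Fisher's exact test at 0.05 with 4 vs 9 records has about 22% power for 25% vs 75%. With 7 vs 15 records it has about 43%. Neither figure includes a penalty for clustering.

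**The case against.** The strongest reply is that 3.3.9a is worded in the singular and sets out no four tests. The 0.05 in 3.4.2 is a general line for the whole study, and how domains are combined, ordered or adjusted could properly sit in an analysis plan that is not shown. This stands. A reader might infer that the protocol plans four separate tests with an 18.5% error rate, but the text does not say so. The 18.5% is conditional and also assumes independence, which is unlikely for domains read from the same visit records.

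A reader might also infer that the randomised comparison is already lost for three domains. Section 3.3.9a fixes no denominator, so an analysis over all sampled adolescents is compatible with it. Section 3.3.9b also plans study-measured office and ambulatory BP in both arms, which could establish BP status whether or not the clinic checked it. The protocol does not link those measurements to the primary outcome, but the selection problem remains a risk of an analysis left open, not a stated plan.

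Nor can the smallest counts be applied to all three domains, because detection and management include elevated BP. The prevalences are background figures; a diagnosis made over three visits need not match single-visit readings. Control facilities also receive the guideline orientation (3.3.8), so 17% may not hold there.

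None of this answers the main point. What counts as the primary outcome belongs in the protocol, and on that 3.3.9a disagrees with 1.10 and 3.3.5. A composite reading does not help: none is defined, and 17% to 34% is the rate of BP checking, not of a composite.

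**Conclusion.** The concern holds as an inconsistency within the protocol: four primary domains in 3.3.9a against one hypothesised and powered endpoint in 1.10 and 3.3.5. The sample size is not in error; it covers one domain of the four.

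Two consequences are conditional. If the domains are tested separately at 0.05, family-wise error could reach 18.5% under independence and at most 20%, and it would be lower with positive correlation or very sparse data. If the last three are analysed only among records with a raised BP, the comparison conditions on a post-randomisation event and rests on about 2–4 vs 4–9 records for high BP and about 7 vs 15 for elevated or high BP. Those counts assume the planned checking rates, the cited prevalences and all 24 facilities retained. Even at an assumed 30% prevalence they reach only about 12 vs 24.

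**What to change.** In 3.3.9a, name one primary outcome: BP recorded at the most recent visit (yes/no), with all sampled adolescents as the denominator. This matches hypothesis 1 and 3.3.5, and the sample size stays as it is.

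Move detection, investigation and management to secondary outcomes. Report each over all sampled adolescents, for example as the proportion with a raised BP recorded and acted on, so that the arms remain comparable as randomised. Such a measure combines recording with response and should be described that way. State in 3.3.9 and 3.4.2 that no confirmatory claim will be made on these three.

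The change is to wording only. The sponsor gives up confirmatory claims on three domains that the design does not power; keeping all four as co-equal primaries would instead need at least 15 facilities per arm under Bonferroni, for BP checking alone.

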### **3.2.2 Study design**

The study will employ a cross-sectional design to describe healthcare workers’ intentions to screen adolescents for hypertension. It will also describe the relationships between the constructs within the theory of planned behaviour (TPB) model. The study will be undertaken in two phases. The first phase will involve the development of a self-administered TPB-based questionnaire to be used for a cross-sectional survey in the second phase. The questionnaire development process will be guided by the “manual for constructing questionnaires based on the theory of planned behaviour” (Francis et al., 2004) and will involve an elicitation study, questionnaire formatting and validity assessment for the questionnaire.

Staff from ART facilities having 20 to 40 adolescents on treatment will be engaged to support the questionnaire development process in the first phase while those from facilities with at least 40 adolescents living with HIV on treatment will be targets for the second phase of the study.

The phases of the non-experimental study are now described.

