#### **d. Recruitment**

The administrators of prospective facilities will be engaged to seek their consent for facility participation. The study will be introduced to healthcare workers in the consenting facilities by the PI during their weekly clinical meetings. An anonymous questionnaire pack with an invitation letter and consent form will be left with the heads of relevant clinical units in the health facilities so they support and encourage the participation of their team members. A drop box will be left at the administration of each facility for completed questionnaires to be dropped in. Weekly reminders will be provided to all prospective respondents to ensure they respond within the survey period. For participants who would like to respond electronically, the link to a google form containing the questionnaire will be shared with them for completion.

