### **3.3.4 Recruitment**

Recruitment into the study will be done at three levels: health facilities, health workers and adolescents living with HIV.

1. **Health facility recruitment**

The PI will invite potential participating clusters (i.e. health facilities) through their respective administrators to participate. In each consenting facility, the PI will identify a primary contact person for the research team.

1. **Clinical staff recruitment**

Once facilities are recruited, the PI will contact the focal persons to obtain details of potential clinical staff who may be interested in participation based on the inclusion and exclusion criteria. The potential participants will be engaged to discuss the study protocol. Those who express interest will be provided with a study invitation pack, including a letter of invitation, information sheet and consent form.

1. **Patient recruitment**

Using a random sequence provided by the study team, a random sample of 20 adolescents living with HIV per facility will be selected for baseline and end-line assessment. The consent of their caregivers will be sought, followed by the adolescents’ consent or assent as may be age-appropriate.

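### The baseline rule does not ensure that the scored visit predates study contact with clinic staff, so the baseline BP-check rate may not describe existing practice

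*Protocol*

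**What the plan says.** Section 3.3.9 (a. Primary outcomes) draws adherence from client care records. For baseline: "At baseline, it will assess the records of 20 randomly selected adolescents who received care at the facility six months prior to the assessment", and the tool will "extract the data from their most recent visit". I read this as a look-back over the six months before the assessment. At follow-up, "data will be extracted from the most recent visit of 20 randomly selected adolescents who received care at the facility after the intervention commenced".

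On staff contact, section 3.3.4 has the investigator obtain details of eligible clinical staff, and then "The potential participants will be engaged to discuss the study protocol"; interested staff receive an information sheet and consent form. Section 3.3.6 says that "allocation will be concealed until the baseline assessment is completed" and that "facilities will not be informed of allocation until after both facilities and individual health workers are identified and recruited", and it equates that point with the end of baseline.

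The survey in section 3.2.6 is a second route of contact. It concerns intention to screen adolescents' BP. "The study will be introduced to healthcare workers in the consenting facilities by the PI during their weekly clinical meetings", data collection may take eight weeks, and reminders go out weekly. On eligibility, section 3.2.2 says "those from facilities with at least 40 adolescents living with HIV on treatment will be targets for the second phase of the study"; section 3.3.2 sets the same threshold for trial facilities.

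The baseline rate bears on research question 1 in section 1.8 (whether providers adhere) and on the first output in section 3.5 (how often BP is screened). Under section 3.3.8, all 24 facilities then receive a guideline orientation.

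**The concern.** A baseline meant to show existing practice should come from visits made before staff knew that BP checks in adolescents were being studied. Here the window ends at the assessment, and within it the most-recent-visit rule picks the visits closest to that date, which are the ones most likely to follow study contact. The protocol's own theory (sections 1.5 and 2.11) holds that a shift in attitudes and perceived norms raises BP checking, so a reaction to being studied is credible.

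At stake is the description of existing adherence. Sections 1.6 and 2.10 justify the study partly because this level is unknown. Baseline is the only measurement taken before every facility is oriented on the guideline, so a distorted baseline cannot be recovered from follow-up data.

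**Working it through.** **1. The plan's own figure.** Section 3.3.5 gives 17% v 34%, 20 adolescents per cluster, ICC 0.05, two-sided 5% and 80% power, hence 10 facilities per arm.

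- n per arm before clustering = [1.96·√(2·0.255·0.745) + 0.842·√(0.17·0.83 + 0.34·0.66)]² / 0.17² = 102.0
- Design effect = 1 + 19·0.05 = 1.95
- Clusters per arm = 102.0 × 1.95 / 20 = 9.95, so 10 (power 0.802)

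The figure reproduces. It concerns the between-arm comparison, and this point does not change it.

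**2. Order of events.**

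| Event | What the protocol fixes |
|---|---|
| Staff engaged and recruited (3.3.4, 3.3.6) | Done by the time allocation is disclosed, which follows baseline; interval to the extraction not given |
| Facility coordinators oriented (Table 2) | Row stands above baseline; months cannot be read in the available copy |
| Survey (3.2.6) | Described before the trial; no row in Table 2; date relative to baseline not given |
| Scored baseline visit (3.3.9) | Latest visit in the six months before the assessment; no reference to contact |

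**3. Share of scored visits after contact.** Let E be the months from first staff contact to extraction and V the interval between visits. The protocol gives neither, so both are assumptions. With visit timing spread evenly, the exposed share is f = min(1, E/V).

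| Contact before baseline | V = 1 month | V = 3 months | V = 6 months |
|---|---|---|---|
| about 1 week | 25% | 8% | 4% |
| 2 weeks | 50% | 17% | 8% |
| 1 month | 100% | 33% | 17% |
| 2 months | 100% | 67% | 33% |
| 3 months | 100% | 100% | 50% |

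**4. Effect on the baseline rate.** Take 17% as the rate without awareness (borrowed from section 3.3.5) and r as the rate after contact (assumed). Observed rate = 17% + f·(r − 17%).

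| f | r = 17% (no reaction) | r = 25.5% |
|---|---|---|
| 17% | 17.0% | 18.4% |
| 33% | 17.0% | 19.8% |
| 67% | 17.0% | 22.7% |
| 100% | 17.0% | 25.5% |

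The distortion runs from nil to the whole reaction (8.5 points in this example), depending on three quantities that the protocol does not give.

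**The case against.** A reader might infer more than the text supports, in four ways.

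- **That the baseline visits do follow staff contact.** The extraction is retrospective over six months. The visits may wholly, partly or not at all predate contact. Nor is the survey shown to come first: the budget lists a questionnaire based on the same theory under the guideline orientation, a row that follows baseline in Table 2. That may be a different use (96 staff, against at least 180 invited to the survey), but the timing stays open. This objection stands, and the point is therefore limited to what the rule fails to ensure.
- **That the trial's main comparison is biased.** It is not, by this route. Hypothesis 1 in section 1.10 compares arms, and contact happens while allocation is concealed, so any reaction is expected in both arms.
- **That a stated before-after result is wrong.** No before-after test of adherence is stated; the only change-over-time hypothesis concerns arterial stiffness. Follow-up visits also take place with staff aware of the study, so a pre-contact baseline would put the awareness effect into any within-arm change. It is better for describing existing practice, but not clearly better for measuring change.
- **That the baseline could rise by the full designed effect, to 34%.** That needs every scored visit exposed and a reaction set equal to the effect the trial is designed to detect. Nothing in the protocol suggests either. Recruitment also covers only about four health workers per facility, so staff outside that group may not react.

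What survives is narrow: no sentence requires the scored visit to predate staff contact, and the most-recent-visit rule leans towards visits after it.

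**Conclusion.** The point holds as a gap in the baseline definition. Awareness of the study could inflate the BP-check rate used to answer research question 1, by anything from about nil to the full reaction of staff. The protocol cannot narrow that range, because it gives neither the contact-to-baseline interval, nor the visit interval, nor the survey date, and the size of any reaction is unknown. The worked figures (18.4% to 25.5% in place of 17%) rest on a three-monthly visit interval, contact two weeks to three months before baseline and a post-contact rate of 25.5%, all assumed. The sample size and the between-arm test are unaffected. The change is worth making because the data are already in the records and baseline is the only look at practice before the guideline orientation.

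**What to change.** In section 3.3.9 (a):

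1. Log for each facility the date of first study contact with ART or outpatient staff, meaning the survey introduction or the staff engagement, whichever is earlier. The invitation to the administrator should not count.
2. Take the baseline adherence rate from the last routine ART visit before that date, within the preceding six months.
3. Keep extracting the most recent visit as well. The adolescent survey in section 3.3.9 (b) validates the records by asking about the latest clinic visit, and the data extraction form records BP at that visit. Replacing it would break the match for every adolescent seen since first contact.
4. State that claims of effect rest on the comparison between arms, because a within-arm change from a pre-contact baseline would include any awareness effect.

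The cost is one logged date per facility, a second visit to extract for some adolescents, and somewhat older baseline visits. The sample size does not change.
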